#### Global Rating of Change Scales

The GRC (7-point scale) will be administered to participants prior to performance-based assessment at 4 weeks and repeated at 3 months. Participants will be asked to answer the following question: ‘How does your overall physical function now compare with your physical function just before you went home from the hospital?’ and respond according to a 7-point scale ranging from 1 = very much improved to 7 = very much worse (Tables 3 and 4)*.* It has previously been reported in the literature that in the case where patients rate their change as ‘minimally improved’, ‘no change’ or ‘minimally worse’, it is unlikely that a clinically important difference has occurred [60]. In this case, these responses will be re-defined as ‘unchanged’ [59, 60]. A clinically important difference will be considered to have occurred if patients rate their change as ‘much worse’, ‘very much worse’, ‘much improved’ or ‘very much improved’, and these will be re-defined as ‘changed’ [60].

**Table 3 Tab3:** Global Rating of Change Scales for overall physical function

How does your overall physical function now compare with your physical function just before you went home from the hospital?	
1. Very much improved 2. Much improved 3. Minimally improved 4. No change 5. Minimally worse 6. Much worse 7. Very much worse

**Table 4 Tab4:** Global Rating of Change Scales for upper arm and body function

How does your arm and upper body function now compare with your arm and upper body function just before you went home from the hospital?	
1. Very much improved 2. Much improved 3. Minimally improved 4. No change 5. Minimally worse 6. Much worse 7. Very much worse	

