### Trial objective and hypothesis

The primary aim of this study is to evaluate the effectiveness of a program of modified sternal precautions on physical function compared with standard care sternal precautions following cardiac surgery via a median sternotomy at 4 weeks post-operatively. We hypothesise that those receiving the modified sternal precautions will have improved physical function at 4 weeks post-operatively compared with participants receiving standard care precautions. The secondary aims are (1) to evaluate the effectiveness of modified sternal precautions compared with standard care on sternal pain and discomfort, kinesiophobia and health-related quality of life (HRQoL) at 4 weeks and 3 months post-operatively, as well as on physical function at 3 months post-operatively; (2) to measure participants’ adherence to sternal precautions; and (3) to explore whether demographic factors, co-morbidities and/or pre, peri- and post-operative risk factors are associated with the development of post-sternotomy complications. This will be an exploratory analysis which may identify trends of predictors reported in the literature [11].

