Key secondary outcomes	2. Patient-identified cardiac pain using numeric and visual prompts, Short Form McGill Pain Questionnaire 2 (SF-MPQ-2), Functional Difficulties Questionnaire (FDQ), grip strength, Tampa Scale of Kinesiophobia shortened version (TSK-11), Medical Outcomes Study 36-item Short Form Health Survey (SF-36v2), Global Rating of Change Scales

*S.M.A.R.T.* Sternal Management Accelerated Recovery Trial

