### Statistical methods

Statistical analyses will be performed by the biostatistician. All data will be analysed using the intention-to-treat principle. Descriptive statistics, including mean and SD, median and interquartile range, number and percent, and frequency will be used to summarise data (depending on distribution and type of data). This also includes participant demographics and adherence to sternal precautions. A comparison between the two hospitals will be conducted on the demographic profile of the participants to establish differences in each presenting population.

The primary outcome—the change from baseline to 4 weeks in the SPPB—will be analysed using a mixed between-and-within subjects analysis of variance with repeated measures across participants. The primary hypothesis will be examined by a contrast evaluating change from baseline to the 4-week time point in the modified sternal precaution group compared with the standard care group. The analysis will be carried out according to the intention-to-treat principle, based on the groups to which participants were randomised. The interactions between group and time will be examined first to assess the effect of intervention, and, if no interaction is present, then group and time main effects will be examined. If there are issues with non-normality or ceiling/floor effects of the SPPB, transformation or dichotomisation will be considered. If there are participants who are not following the assigned group protocol, we will consider a supplementary per-protocol analysis. Key secondary outcome data (including upper limb function, pain, kinesiophobia and HRQoL) will be summarised and analysed similarly to the primary outcome.

Logistic regression will be used to determine pre-, peri- and post-operative risk factors associated with the development of post-sternotomy complications. This will be an exploratory analysis which may identify trends of predictors reported in the literature having an individual effect on post-operative sternal complications (i.e., female sex, diabetes mellitus, obesity, bilateral internal mammary artery grafts, re-operation for post-operative complications, and blood product requirement were reported as significant predictors of sternal infection). For all tests conducted, a *p* value <0.05 (two-tailed) will be considered statistically significant, and mean differences (95% confidence intervals) will be reported.

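### The Global Rating of Change recode puts 'much worse' and 'much improved' in one 'changed' category, so the derived variable of this secondary outcome has no direction

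*Protocol article*

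**What the plan says.** Under its own heading in the outcomes section, the article describes the GRC as a "7-point scale ranging from 1 = very much improved to 7 = very much worse". It is "administered to participants prior to performance-based assessment at 4 weeks and repeated at 3 months". Table 3 asks about overall physical function and Table 4 about arm and upper body function, both relative to just before discharge.

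The same section then fixes a recode. For minimally improved, no change and minimally worse, the rule is: "In this case, these responses will be re-defined as ‘unchanged". For the remaining four ratings it is: "much worse’, ‘very much worse’, ‘much improved’ or ‘very much improved’, and these will be re-defined as ‘changed". The second class is the article's definition of a clinically important difference.

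Table 1 names the GRC at the end of its key secondary outcomes: "Medical Outcomes Study 36-item Short Form Health Survey (SF-36v2), Global Rating of Change Scales". Statistical methods says that key secondary outcome data "will be summarised and analysed similarly to the primary outcome". The examples given there in brackets do not include the GRC, but they are introduced as examples. No section divides 'changed' into better and worse or gives another purpose for it.

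**The concern.** The scale has two directions and the recode removes the distinction between them. A patient who reports being very much worse receives the same value as one who reports being very much improved.

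The trial's questions are directional. The main hypothesis is that "those receiving the modified sternal precautions will have improved physical function at 4 weeks post-operatively" compared with standard care, and the Discussion adds the expectation that the modified precautions will cause no harm. A 'changed' indicator informs neither statement. If the arms differ on it, the reader cannot tell which arm did better; if they do not differ, the reader cannot tell whether gains in one arm are offset by losses in the other.

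This is not a detail left for a fuller document. The article states the rule, and it is the rule an analyst would apply as written.

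**Working it through.** **Inputs.** From the article: scale values 1 to 7, with 1 the best and 7 the worst; 'unchanged' = 3, 4, 5; 'changed' = 1, 2, 6, 7; 36 participants per group randomised and 29 per group required before the dropout allowance. The article gives no expected GRC distribution and no figure for this outcome, so there is nothing to reproduce. All shares below are assumptions.

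**Identity.** In each arm let I be the share rated 1–2 and W the share rated 6–7. The recoded outcome is C = I + W. Writing Δ for intervention minus control:

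ΔC = ΔI + ΔW

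Benefit (ΔI > 0) and harm (ΔW > 0) enter with the same sign. A measure that kept direction would give them opposite signs or report them apart.

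**Four assumed cases** (percent; differences in percentage points):

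| Case | Control I / W | Intervention I / W | C control | C intervention | ΔC | ΔI | ΔW |
|---|---|---|---|---|---|---|---|
| A | 60 / 5 | 40 / 25 | 65 | 65 | 0 | −20 | +20 |
| B | 40 / 25 | 60 / 5 | 65 | 65 | 0 | +20 | −20 |
| C | 60 / 5 | 75 / 5 | 65 | 80 | +15 | +15 | 0 |
| D | 60 / 5 | 60 / 20 | 65 | 80 | +15 | 0 | +15 |

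Cases A and B are opposite effects, and both give no difference. Cases C (benefit only) and D (harm only) give the same positive difference. The recoded variable cannot separate A from B or C from D.

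**How large the loss can be.** Rearranging the identity, ΔC − ΔI = ΔW: the 'changed' difference misstates the 'improved' difference by exactly the between-arm difference in worsening. If no more than a share w of either arm is worse, the misstatement is at most w:

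- w = 0: no loss; 'changed' is the same as 'improved'.
- w = 5%: at most 5 points, which is 0.05 × 36 = 1.8 patients per arm (0.05 × 29 = 1.45 on the smaller count).
- w = 20%: at most 20 points, which is 0.20 × 36 = 7.2 patients per arm (0.20 × 29 = 5.8).

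**With direction kept.** Using the same cut-points in three classes, case A reads 20 points fewer improved and 20 points more worse on the intervention; case B reads the reverse. C and D separate in the same way.

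**The case against.** The strongest reply is that the article never states a between-arm test of 'changed'. The section sets a threshold for clinically important change, and the GRC is not among the outcomes named in Statistical methods. An analysis plan that is not shown may use it differently. This stands in part: the analysis is unstated. But the GRC is listed as a key secondary outcome, no other use is given, and the defect is in the variable's definition, so it carries into any comparison of arms made on that variable.

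A second reply is that the coding follows cited work. The threshold can be kept in full: three classes use the same cut-points and only undo the merging of directions.

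A third is that few patients will be much worse at 4 weeks or 3 months than just before leaving hospital after a sternotomy. This is plausible, and the loss would then be small, as the w = 5% line shows. It limits the consequence but does not justify the rule.

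Three stronger readings are tempting and are not supported:

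- A reader might infer that the GRC cannot show benefit or harm at all. Direction is lost only in the derived variable. The seven-category responses are collected, nothing says they will be discarded, and the planned summaries by number and percent could present them.
- A reader might infer that the recode biases an anchor-based estimate of important SPPB change. No section uses the GRC as an anchor; the 2-point minimal important difference is taken from prior research.
- A reader might infer that harm would go unseen in the trial. Sternal infection, re-wiring, re-operation and readmission are recorded, the modified Sternal Instability Scale is applied, and the monitoring committee reviews serious adverse events.

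**Conclusion.** The point holds for the recoded GRC. As written, the rule yields a variable in which a difference between arms has no direction and equal rates can hide opposite effects. That follows from C = I + W and does not depend on the illustrative shares. The size in practice does depend on an unknown: the loss equals the between-arm difference in the share rating themselves worse. It runs from nothing when nobody is worse, through at most 5 points if worsening is capped at 5% per arm, to 20 points in the assumed offsetting case.

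This is a minor correction to one secondary outcome. The raw responses, the SPPB analysis, the sample size and the remaining secondary and safety measures do not rest on this recode.

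**What to change.** Replace the two-class recode with three classes at the same thresholds: improved (1–2), unchanged (3–5) and worse (6–7). Report the improved and worse proportions separately by arm, for both questions (Tables 3 and 4), at 4 weeks and at 3 months. An ordinal analysis of the full 7-point score is an acceptable alternative but is not required.

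The cost is one changed recoding rule and a few added table rows. The article says that follow-up was completed in April 2017, but the responses needed are part of what the plan collects. The change should be recorded before any unblinded analysis of the GRC; if that has begun, it should be disclosed as made afterwards.

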### Sample size

Sample size calculations were performed for the primary outcome: SPPB. On the basis of acute care in-patient populations and using the MID between the treated group of 2 points of a total possible score of 12 points, with an SD of 2.7 points [36], it is anticipated that 29 participants are required per group (58 in total), based on a two-sample *t* test. This was based on a type I error rate of 0.05, which is consistent with recommendations and a power of 0.80 [61]. This sample was increased to 72 participants on the basis of a predicted 20% dropout rate, based on our previous study in the same population conducted at both participating hospitals [17].

### Data management and quality

We will use the online REDCap database (https://redcap.healthinformatics.unimelb.edu.au/) supported by the University of Melbourne. High data quality will be aimed for through training of those who collect, check and enter study data as well as by regular data checks for inconsistency between and within measurements and missing data. A check will be performed to evaluate the correctness of the randomisation before the start of the statistical analysis. The data and safety monitoring committee (DSMC), with two independent clinical members and one independent statistician, will act in an advisory capacity for the clinical investigators to monitor withdrawals and review ethical conduct and serious adverse events. Further details will be provided in the DSMC charter, once it is developed.

### Statistical methods

Statistical analyses will be performed by the biostatistician. All data will be analysed using the intention-to-treat principle. Descriptive statistics, including mean and SD, median and interquartile range, number and percent, and frequency will be used to summarise data (depending on distribution and type of data). This also includes participant demographics and adherence to sternal precautions. A comparison between the two hospitals will be conducted on the demographic profile of the participants to establish differences in each presenting population.

The primary outcome—the change from baseline to 4 weeks in the SPPB—will be analysed using a mixed between-and-within subjects analysis of variance with repeated measures across participants. The primary hypothesis will be examined by a contrast evaluating change from baseline to the 4-week time point in the modified sternal precaution group compared with the standard care group. The analysis will be carried out according to the intention-to-treat principle, based on the groups to which participants were randomised. The interactions between group and time will be examined first to assess the effect of intervention, and, if no interaction is present, then group and time main effects will be examined. If there are issues with non-normality or ceiling/floor effects of the SPPB, transformation or dichotomisation will be considered. If there are participants who are not following the assigned group protocol, we will consider a supplementary per-protocol analysis. Key secondary outcome data (including upper limb function, pain, kinesiophobia and HRQoL) will be summarised and analysed similarly to the primary outcome.

Logistic regression will be used to determine pre-, peri- and post-operative risk factors associated with the development of post-sternotomy complications. This will be an exploratory analysis which may identify trends of predictors reported in the literature having an individual effect on post-operative sternal complications (i.e., female sex, diabetes mellitus, obesity, bilateral internal mammary artery grafts, re-operation for post-operative complications, and blood product requirement were reported as significant predictors of sternal infection). For all tests conducted, a *p* value <0.05 (two-tailed) will be considered statistically significant, and mean differences (95% confidence intervals) will be reported.

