### Withdrawal from trial

All participants will be followed after their surgery and measured. Every attempt will be made to accommodate individual requirements to facilitate attendance at follow-up time points beyond discharge from hospital (i.e., taxi vouchers, flexible dates, appointment times). Participants will be withdrawn if they withdraw their consent, and this will be reported. Data collected until this time will be included.

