### Data collection

Demographic data as well as pre-, intra- and post-operative variables will be collected as listed in Table 2. Data will be collected from the participants and their medical records. All baseline assessments will be performed at the same time of day (08:00–17.00) for each participant in the post-operative period at day 4 (±1 day) in the in-patient setting across centres to minimise potential bias in recruiting participants. The follow-up, outpatient testing at 4 weeks (±14 days) and 3 months (±14 days) will take place in the research room at RMH (Fig. 2). An independent and trained assessor (located off-site) who is blinded to allocation will conduct all measurement sessions. All tests and questionnaires will be administered face-to-face by the outcome assessors and carried out at 4 weeks and 3 months post-operatively to ensure consistency across participants. Post-hospital discharge follow-up will be conducted via phone. If participants are unable to be contacted by phone for a period of 14 consecutive days from the assessment due date, they will be considered lost to follow-up for purposes of post-discharge outcome measurement.

**Table 2 Tab2:** Data collection details

Demographic data • Name and contact details • Date of birth • Sex • Marital status • Height and weight • Occupation status • Education status • Smoking history • Past medical history and comorbidity index (Charlson comorbidity index) • Functional history (including pre-morbid functional level, use of gait aids, dominant upper limb) • Date of admission to and discharge from acute setting	

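### If the primary repeated-measures ANOVA is fitted complete-case over all three visits, patients missing at 3 months leave the 4-week comparison, against the protocol's own rule on data already collected

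*Protocol article*

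**What the plan says.** All statements are from the Protocol article.

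- **Method (Statistical methods).** The primary outcome "will be analysed using a mixed between-and-within subjects analysis of variance with repeated measures across participants". The group-by-time interaction is examined first, and "The primary hypothesis will be examined by a contrast evaluating change from baseline to the 4-week time point". Key secondary outcomes are to be analysed in a similar way.
- **Analysis set (Statistical methods).** "All data will be analysed using the intention-to-treat principle". The same section later describes the analysis as being "according to the intention-to-treat principle, based on the groups to which participants were randomised".
- **Partial data (Withdrawal from trial).** For participants who withdraw consent: "Data collected until this time will be included".
- **Visits (Data collection).** Baseline is at post-operative day 4. "The follow-up, outpatient testing at 4 weeks (±14 days) and 3 months (±14 days) will take place in the research room at RMH".
- **Dropout (Sample size).** The calculation uses a difference of "2 points of a total possible score of 12 points, with an SD of 2.7 points", giving 29 per group. "This sample was increased to 72 participants on the basis of a predicted 20% dropout rate".

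The article does not say whether the 3-month score is a level of the primary model, how the model is estimated, or when during follow-up the 20% is expected to be lost.

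**The concern.** A mixed between-within ANOVA in its classical form, as usually run, needs a value from every patient at every level of the time factor. A patient with one missing level is deleted from the whole analysis.

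Three features of the protocol point to a three-level time factor:

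- The interaction test and the baseline-to-4-week contrast are described as separate steps. With only two time points they would be the same test.
- The SPPB is scheduled at three visits.
- Physical function at 3 months is a stated secondary aim, and no other model is named for it.

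On that reading, a patient who attends at 4 weeks and is then lost contributes nothing to the primary 4-week contrast, although both scores that the contrast needs were observed. Membership of the primary analysis then depends on an event after the primary time point. If late loss is related to function, the comparison is made on a selected group.

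A second, smaller issue concerns the error term. The classical ANOVA can test the contrast against one within-subject error pooled over all visits, which is valid only under sphericity. The visits are unequally spaced (day 4, 4 weeks, 3 months), so two later scores may well correlate more with each other than with the early post-operative one.

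**Working it through.** **Inputs.** Difference 2 points, SD 2.7, two-sided 5% level, power 80%, 1:1 allocation, 72 randomised, 20% dropout: all from the article. The SD is taken, as the plan takes it, as that of the quantity compared by the two-sample t test. The timing of dropout and the correlations between visits are assumptions.

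**1. The plan's own figure.** n per group = 2 × (1.96 + 0.8416)² × (2.7/2)² = 2 × 7.849 × 1.8225 = 28.6, so 29, or 58 in total. The exact t calculation gives 29.6. Inflation: 58/0.8 = 72.5, so 73. The stated 29 per group and 72 reproduce to within rounding.

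**2. Complete-case analysis over three visits.** 72 × 0.8 = 57.6 patients, or 28.8 per arm. Standard error = 2.7 × √(2/28.8) = 0.7115, and 2/0.7115 = 2.811. Power = Φ(2.811 − 1.96) = 80.3% (exact t: 78.9%). This is about the planned level.

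**3. What is discarded.** Let f be the share of the 14.4 losses that falls after week 4. Patients with a 4-week score number 72 − 14.4 × (1 − f). The three-visit complete-case analysis discards 14.4 × f of them.

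| f | With 4-week score | Discarded | Power using all 4-week scores | Power, complete-case |
|---|---|---|---|---|
| 0 | 57.6 | 0 | 80.3% | 80.3% |
| 0.25 | 61.2 | 3.6 | 82.6% | 80.3% |
| 0.5 | 64.8 | 7.2 | 84.6% | 80.3% |
| 0.75 | 68.4 | 10.8 | 86.5% | 80.3% |
| 1 | 72.0 | 14.4 | 88.2% | 80.3% |

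Power forgone runs from 0 to 88.2 − 80.3 = 7.9 points. Exact t figures at 28.8, 32.4 and 36 per arm are 78.9%, 83.5% and 87.3%.

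**4. Possible bias (illustration only).** Dropout after week 4 was simulated as logistic in the 4-week score, with slopes of 0.5 to 1.5 per SD and correlations of 0.3 (baseline with each later visit) and 0.7 (4 weeks with 3 months). If loss depends on function in the control arm only, the complete-case contrast is shifted by about −0.18 to −0.43 points when 20% are lost late, and by about −0.09 to −0.24 when 10% are. If one mechanism acts in both arms and the benefit is real, the difference is understated.

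**5. Pooled error (illustration only).** Using the same correlations and variance 2.7² = 7.29 at each visit:

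- Variance of the baseline-to-4-week change: 2 × 7.29 × 0.7 = 10.21.
- Average over the three pairs of visits: (10.21 + 10.21 + 4.37)/3 = 8.26.
- Ratio: 8.26/10.21 = 0.81, which does not depend on the SD.

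A test against pooled error therefore uses a standard error √0.81 = 0.90 times the correct one. With 29 per arm the pooled error has 2 × 56 = 112 degrees of freedom and a critical value of 1.98. The effective cut-off is 1.98 × 0.90 = 1.78, a two-sided error of about 7.5%. Simulations gave 7.6% to 7.8%. A test of the contrast against its own error gave 4.8% to 5.1%.

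**The case against.** The strongest reply is that the article never says the model is complete-case or that it includes 3 months. The primary outcome is defined as change from baseline to 4 weeks, and the Abstract describes the repeated-measures ANOVA in the same terms. An ANOVA on those two visits fits the words, discards no observed 4-week change and satisfies sphericity trivially. Missing-data rules may also sit in an analysis plan that is not shown. This stands as a limit: the loss is conditional on a three-visit, complete-case fit. It does not remove the point, because the method named is the one that usually behaves this way and the separate contrast suggests a third visit.

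A reader might infer three stronger things that the documents do not support:

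- **That the analysis breaks intention-to-treat.** Statistical methods explains the term as analysis by randomised group, which a complete-case ANOVA respects. The firmer conflict is with the Withdrawal section. Strictly, that rule concerns patients who withdraw consent. Patients who simply miss the 3-month visit fall under its evident intent, not its letter.
- **That the trial is underpowered.** The sample of 72 already pays for the 20% loss.
- **That a particular bias or type I error is established.** The shifts in step 4 need selective loss in one arm, for which the protocol gives no basis, and the upper end needs all losses to fall after week 4. The 7.5% needs assumed correlations and a pooled error term.

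Patients lost before week 4 have no 4-week score to discard under any method.

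**Conclusion.** The point holds in conditional form. The protocol fixes a method which, on its natural reading and in its usual complete-case form, cannot honour the protocol's own rule that data gathered before withdrawal are kept. The size is 0 to 14.4 of 72 observed 4-week scores discarded and 0 to about 8 points of power forgone. It rests on 20% loss over the whole follow-up, with an unknown share after week 4. Power against the plan's own target is not materially affected. Bias is possible if late loss depends on function, but its direction and size cannot be determined from the article. The sphericity issue arises only if the contrast is tested against pooled error. Because the method concerns the primary outcome and carries over to the key secondary outcomes, it is worth correcting.

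**What to change.** Replace the ANOVA with a likelihood-based linear mixed model for repeated measures: REML, unstructured covariance over visits, Kenward-Roger degrees of freedom and group-by-visit terms. It should use all available scores from every randomised patient. Name the 4-week group contrast in change from baseline as the primary test, and use the same model for the continuous secondary outcomes. This keeps every observed 4-week score, agrees with the Withdrawal section and drops the sphericity assumption. It remains valid when loss depends on scores already observed, though not when it depends on unobserved ones.

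At minimum, if the ANOVA is kept, state that the primary analysis uses baseline and week 4 only, so that no observed 4-week change is dropped, and analyse 3 months separately.

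The cost is a few sentences of analysis wording and a standard software procedure. No new data are needed and the sample size is unchanged. Follow-up is reported as complete, so the change should be recorded, with its date, as made before or after unblinding.

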### Trial intervention

The implementation of the sternal precautions is performed by the same ward physiotherapist according to allocation for both groups. There will be a different physiotherapist for each participating hospital providing the intervention for both groups. Both physiotherapists are senior clinicians with over 5 years of clinical experience in cardiac surgery. Training will be provided by one independent physiotherapist to ensure consistency in each institution. Standard care is consistent across centres.

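### The primary SPPB contrast uses raw change without adjusting for baseline; adjustment is a free gain in precision, and the sample-size section does not say which SD the 2.7 is

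*Protocol article*

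**What the plan says.** In the protocol article, Statistical methods defines the primary outcome as the change in SPPB between baseline and 4 weeks. It analyses this by a mixed between-and-within analysis of variance with repeated measures: "The primary hypothesis will be examined by a contrast evaluating change from baseline to the 4-week time point", compared between the two groups. Baseline SPPB is not named as a covariate.

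Sample size plans for a two-sample t test, "using the MID between the treated group of 2 points of a total possible score of 12 points", and "with an SD of 2.7 points [36], it is anticipated that 29 participants are required per group". The error rates are given as "This was based on a type I error rate of 0.05" and "a power of 0.80", and Statistical methods makes the test two-sided: "value <0.05 (two-tailed) will be considered statistically significant". The total of 58 is raised to 72 for 20% dropout. The section mentions neither change scores nor a correlation between visits.

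Trial design and Randomisation and allocation both place baseline testing before allocation. Data collection puts baseline at post-operative day 4 (±1 day) and the first follow-up at 4 weeks (±14 days). The primary outcome section quotes SPPB intra-class correlations of 0.88 to 0.92 for measures one week apart and 0.78 as a 6-month average, from the same reference as the SD.

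**The concern.** With two visits and complete data, the group-by-time contrast is a comparison of mean raw change between arms. That fixes the coefficient of baseline at 1. Baseline adjustment estimates the coefficient instead, and with equal SDs at the two visits its value is r. Fixing it at 1 adds noise unless r is near 1.

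Two things follow. Precision is given up although the variable needed to recover it is already collected. And the sizing does not connect to the analysis: a t test with SD 2.7 describes the planned contrast only if 2.7 is the SD of change. If it is the SD of a score at one visit, the power of the planned contrast depends on a correlation that the protocol does not give. Baseline is early in hospital recovery and follow-up falls roughly 2 to 6 weeks after surgery, so that correlation could be modest.

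**Working it through.** **Inputs.** Difference 2 points, SD 2.7, two-sided alpha 0.05, power 0.80, 29 per group (Sample size; Statistical methods for the two-sided test). The correlation r between baseline and 4-week SPPB is not in the document for this setting. It is an assumption, shown from 0 to 0.78.

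**Step 1: the plan's own figure.** Normal approximation: n = 2 × (1.96 + 0.8416)² × 2.7² / 2² = 2 × 7.849 × 7.29 / 4 = 28.6, so 29 per group, with power 80.5%. By exact non-central t, 29 per group gives 79.2%, and 30 are needed for 80%. Dropout: 58 / 0.8 = 72.5, against 72 stated. The figure reproduces within rounding.

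**Step 2: if 2.7 is the SD of a score at one visit, equal at both visits.**
- SD of change = 2.7 × √(2(1 − r)). This equals 2.7 at r = 0.5 and is larger below that.
- Residual SD after baseline adjustment = 2.7 × √(1 − r²). This never exceeds 2.7.
- Variance ratio, adjusted to change = (1 − r²) / (2(1 − r)) = (1 + r)/2.

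Worked case, r = 0.3, 29 per group, with √(2/29) = 0.2626:
- Change: SD 2.7 × √1.4 = 3.19; SE 3.19 × 0.2626 = 0.84; non-centrality 2/0.84 = 2.38; power 64.9% (56 df).
- Adjusted: SD 2.7 × √0.91 = 2.58; SE 0.68; non-centrality 2.96; power 82.8% (55 df).

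The same calculation over the range (exact t, 29 per group; the last column is n per group for 80% power):

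| r | SD change | Power, change | SD adjusted | Power, adjusted | n for 80%, change / adjusted |
|---|---|---|---|---|---|
| 0 | 3.82 | 50.0% | 2.70 | 79.1% | 59 / 30 |
| 0.2 | 3.42 | 59.2% | 2.65 | 80.7% | 47 / 29 |
| 0.3 | 3.19 | 64.9% | 2.58 | 82.8% | 42 / 28 |
| 0.4 | 2.96 | 71.6% | 2.47 | 85.6% | 36 / 26 |
| 0.5 | 2.70 | 79.2% | 2.34 | 89.2% | 30 / 23 |
| 0.6 | 2.41 | 87.3% | 2.16 | 93.4% | 24 / 20 |
| 0.78 | 1.79 | 98.7% | 1.69 | 99.3% | 14 / 13 |

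**Step 3: if 2.7 is already the SD of change.** The change contrast has the planned power at every r (79.2% exact, 80.5% by normal approximation). The adjusted SD is 2.7 × √((1 + r)/2):

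| r | SD adjusted | Power, adjusted |
|---|---|---|
| 0 | 1.91 | 97.5% |
| 0.3 | 2.18 | 93.0% |
| 0.5 | 2.34 | 89.2% |
| 0.78 | 2.55 | 83.6% |

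Adjustment gains under either reading. A power shortfall of the change contrast arises only under the first, and only below r = 0.5 at 29 per group.

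**The case against.** The strongest reply is that nothing here is an error. A change contrast is valid and unbiased under randomisation, and preferring analysis of covariance is a matter of efficiency. That stands. A reader might infer bias from chance baseline imbalance, but such imbalance is already part of the variance of the change score. It is not a second defect on top of lost power. The SE of the baseline difference is 2.7 × √(2/29) = 0.71 at 29 per group and 2.7 × √(2/36) = 0.64 at 36.

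A reader might also infer that the trial is underpowered. The document does not support that. It needs two unproven assumptions: that 2.7 is a single-visit SD and that r is below 0.5. The only SPPB correlations quoted (0.78 to 0.92) lie well above 0.5, and there the two analyses hardly differ if 2.7 is a single-visit SD. They are reliability figures, not the correlation between day 4 after sternotomy and 4 weeks, so a lower value cannot be excluded, but no figure in the document points to one. A baseline mean depressed by surgery does not by itself lower the correlation.

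Two technical limits also stand. The 0.5 threshold assumes the full dropout allowance; with all 36 per group retained, the change contrast reaches 80% at about r = 0.4. And if the repeated-measures model includes the 3-month visit with a pooled error term, its power will not be exactly that of the two-visit comparison.

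Finally, it may be tempting to ask for hospital as a factor, since "There will be a different physiotherapist for each participating hospital providing the intervention for both groups". That same sentence weakens the case: each physiotherapist treats both arms, so therapist is not confounded with allocation.

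**Conclusion.** This is a free improvement, not a flaw that invalidates the trial. The protocol fixes a raw change contrast and leaves unused a covariate measured in everyone before allocation. The contrast is unbiased, but less precise than a baseline-adjusted comparison unless r is close to 1: with equal SDs at both visits, adjustment multiplies the variance by (1 + r)/2.

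The sizing does not settle whether the planned contrast delivers the stated power, because "with an SD of 2.7 points" is not tied to a score or to a change. The wording, next to the total possible score, leans towards a score but does not say so. At r = 0.3 and 29 per group, adjustment moves power from 65% to 83% if 2.7 is a single-visit SD, and from 79% to 93% if it is the SD of change. At r = 0.78 with a single-visit SD, the gain is under 1 percentage point. These results rest on equal SDs at both visits, complete data on 29 per group and an assumed r. A shortfall below 80% is possible, not shown.

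**What to change.** 1. Make the primary estimate the 4-week between-group difference in SPPB adjusted for baseline SPPB, by analysis of covariance or by a longitudinal model with a common baseline mean for both arms.
2. In Sample size, state whether 2.7 is the SD of a single-visit score or of change, as the cited source gives it. Do not relabel it as a baseline-adjusted SD: nothing in that section supports this.
3. No hospital term is needed on this account.

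No new data are needed, since both variables are collected. Recruitment ended in November 2016 and follow-up in April 2017, so the sample size cannot change. The cost is more than wording: this replaces the primary analysis after data collection, so it must be decided before any unblinded analysis and recorded, with its date and reason, as a change to the plan.
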